# Anakinra Pilot – a clinical trial to demonstrate safety, feasibility and pharmacokinetics of interleukin 1 receptor antagonist in preterm infants

**DOI:** 10.3389/fimmu.2022.1022104

**Published:** 2022-10-27

**Keywords:** preterm infant, inflammation, anti-inflammatory therapy, interleukin 1 receptor antagonist, clinical trial, translational research, drug repurposing, protocol anakinra pilot

## Abstract

**Background:**

Bronchopulmonary dysplasia (BPD), its complication pulmonary hypertension (BPD-PH) and preterm brain and gut injury lead to significant morbidity and mortality in infants born extremely prematurely. There is extensive evidence that the pro-inflammatory cytokine interleukin 1 (IL-1) plays a key role in the pathophysiology of these illnesses. Two decades of clinical use in paediatric and adult medicine have established an excellent safety and efficacy record for IL-1 blockade with IL-1 receptor antagonist (IL-1Ra, medication name anakinra). Building on robust pre-clinical evidence, the Anakinra Pilot trial aims to demonstrate safety and feasibility of administering anakinra to preterm infants, and to establish pharmacokinetics in this population. Its ultimate goal is to facilitate large studies that will test whether anakinra can ameliorate early-life inflammation, thus alleviating multiple complications of prematurity.

**Methods and analysis:**

Anakinra Pilot is an investigator-initiated, single arm, safety and feasibility dose-escalation trial in extremely preterm infants born between 24 weeks 0 days (24^0^) and 27^6^ weeks of gestational age (GA). Enrolled infants will receive anakinra intravenously over the first 21 days after birth, starting in the first 24 h after birth. In the first phase, dosing is 1 mg/kg every 48 h, and dosage will increase to 1.5 mg/kg every 24 h in the second phase. Initial anakinra dosing was determined through population pharmacokinetic model simulations. During the study, there will be a interim analysis to confirm predictions before undertaking dose assessment. Anakinra therapy will be considered safe if the frequency of adverse outcomes/events does not exceed that expected in infants born at 24^0^-27^6^ weeks GA.

**Clinical Trial Registration:**

https://clinicaltrials.gov/, identifier NCT05280340.

## Introduction

Neonatal care has dramatically improved the survival of extremely premature newborn infants over the past 20 years. However, as a result, we face the high price of a steadily rising incidence in a number of morbidities, in virtually all of which inflammation plays a crucial pathophysiological role (1–5). The potent pro-inflammatory cytokine interleukin 1 (IL-1) is a key mediator of these inflammatory processes, as described below. Common examples of such inflammation-driven morbidities are bronchopulmonary dysplasia (BPD) (5), pulmonary hypertension associated with BPD (BPD-PH) (6), cerebral diffuse white matter injury (dWMI) and necrotising enterocolitis.

BPD is a chronic lung disease that can have devastating short- and long-term consequences, including impaired pulmonary and cardiovascular health and adverse neurodevelopmental outcomes (7, 8). BPD has become the most common chronic cardiopulmonary disease in infants, and, together with its gravest complication, BPD-PH, now represents a major burden for affected babies, their families, and health services alike (9). The costs of treating BPD are immense, and were estimated at US$1.7 billion per year in the USA alone in 2009 (10). Recognising that BPD and BPD-PH are inflammatory diseases, the American Academy of Pediatrics (AAP) issued an urgent call for new anti-inflammatory therapies for BPD in 2006 (11). With no safe and effective therapy forthcoming, BPD remains one of the greatest unmet challenges neonatology faces today; hence, the AAP renewed its call to escalate research efforts into the development of new anti-inflammatory strategies to offer a brighter prospect to the tiny patients and their families in 2014 (12).

Yet another morbidity of prematurity that results from a combination of systemic and local inflammation is diffuse white matter injury of the brain (dWMI). dWMI is defined by inflammation, scarring and loss/impaired development of the white matter, and it affects up to 40% of extremely preterm infants (2, 3), resulting in a variety of neurocognitive impairments that manifest in early childhood and persist into adulthood (13). In extremely preterm infants, the cerebral white matter, which contains axons that are insulated by myelin to facilitate rapid conduction of action potentials within and between neurons, is undergoing a period of rapid development and change. The precursor oligodendrocytes that populate the white matter and are ultimately responsible for ensheathing axons with myelin, are exquisitely sensitive to inflammation (14). Inflammatory damage to the vulnerable pre-oligodendrocytes results in dWMI with impairment of myelination, and ultimately neurodevelopmental impairment. Recent evidence has demonstrated that inflammatory white matter injury can persist into the postnatal period for up to 21 days (15).

Despite substantial advances in neonatal medicine over the past three decades, there is still no safe and effective therapy to prevent or at least treat inflammation-driven cardio-respiratory and cerebral injury in preterm infants. The antecedents of BPD (5, 16), BPD-PH (4, 6), and dWMI (2) include oxygen toxicity, fetal and postnatal infection or damaging mechanical ventilation, whose effects are mediated through a common pathway of inflammation. IL-1 is a key pathophysiological culprit in this process; it is highly associated with adverse outcomes in clinical cohorts (17–19), and its pathogenic role has been confirmed in a variety of clinically relevant models of BPD and BPD-PH in neonatal mice, piglets and rats, as reviewed in (20, 21), and in a model of inflammation-induced dWMI in fetal sheep (1, 22).

Interleukin-1 receptor antagonist (IL-1Ra) is an endogenous cytokine that binds to the receptor by which IL-1α and IL-1β exert their pro-inflammatory activities, thus competitively inhibiting their activity. Anakinra is a recombinant protein that is nearly identical to endogenous IL-1Ra. In rodent, piglet and sheep models of early life disease, treatment with exogenous IL-1Ra alleviated the loss of alveolar and pulmonary vascular tissue that characterises BPD, and the accompanying systemic and local inflammation (5, 6). These data are supported by reports in infants and animals, which show that there can be an imbalance between IL-1 and endogenous IL-1Ra that may contribute to prolonged inflammation and eventually neonatal diseases of the lung, heart and brain (23, 24). Moreover, in preterm fetal sheep, infusion of IL-1Ra mitigated brain inflammation and preoligodendrocyte loss that are characteristic of dWMI (22).

As anakinra, IL-1Ra has been used clinically for over 20 years, in more than 200,000 patients, including children and infants. This substantial clinical experience has demonstrated a highly favourable safety profile for anakinra (e.g (25, 26); hence, this medication, which is well established in most other age groups, represents a potential strategy for preventing or treating inflammation, including that underpinning BPD, BPD-PH and dWMI, in infants born prematurely.

Anakinra Pilot, whose full name is “A Clinical Trial to Demonstrate Safety, Feasibility and Pharmacokinetics of Interleukin 1 Receptor Antagonist in Preterm Infants”, is a Phase I/IIa trial designed to establish safety, feasibility and pharmacokinetics of early administration of anakinra to infants born <28 weeks’ gestation.

## Methods and analysis

### Primary aim

To determine safety and feasibility of administering anakinra to premature infants born between 24 weeks and 0 days (24^0^) and 27^6^ weeks of gestational age (GA) from day 1 to day 21 after birth.

### Study type

Investigator-initiated single-arm, Phase I/IIa dose-escalation safety trial.

### Site

Monash Newborn, Monash Children’s Hospital, Monash Health, Melbourne, VIC, Australia.

### Inclusion criteria

• Born between 24^0^ and 27^6^ weeks of GA• Born at on-site at the participating hospital.

### Exclusion criteria

• Inability of the legal guardians to consent.• Any disease or condition that the investigators judge could confound the trial results; these include, but are not limited to, genetic syndromes, severe cardiac or other abnormalities, substantial pre-/perinatal compromise (postnatal hypoxia (SaO2<80% for >3h), intrauterine stroke and others.• Imminent death.• Foreseeable inability to adequately excrete anakinra, i.e. severely and permanently compromised renal function.

### Secondary objectives

1. To conduct an interim pharmacokinetic analysis to compare observed concentrations with predictions from population PK simulation; and

2. To monitor changes of the plasmatic and cellular immune function conferred by treatment with anakinra.

### Sample size

We will recruit 24 infants. Given the well-established, favourable safety profile and extensive clinical experience with anakinra, including in children and infants, as well as detailed knowledge on its mechanism of action, this number of participants will suffice to demonstrate safety and feasibility. In addition, it will allow confirmation of predicted/simulated drug disposition, by comparing observed concentration with the population PK simulation, to inform dose selection for future large effectiveness trials.

### Definitions

#### Safety

For the purposes of the trial’s primary objective, safety will be defined as completion of the described treatment regimen in our target population, without any adverse events of greater frequency or severity than expected to be observed in this high-risk population. For example, at Monash Newborn the baseline rate of late-onset sepsis in this population is 27%, early-onset sepsis is 1%, death is 15%, BPD is 70% and necrotising enterocolitis is 12%.

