### Duration of trial

Assuming rates of admission do not change dramatically, and a recruitment rate of 20-25% of eligible babies, we will be able to enrol 8-15 patients per year; hence, we expect completion of enrolment in 24 months.

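### The safety criterion makes no allowance for sampling error: with 24 infants a drug with no effect would usually fail it, and a result that just meets it does not rule out doubled death or necrotising enterocolitis

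*Protocol article*

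**What the plan says.** The Safety definition in the protocol article ties the primary objective to completion of treatment "without any adverse events of greater frequency or severity than expected to be observed in this high-risk population". The Abstract (Methods and analysis) puts it as a decision: "Anakinra therapy will be considered safe if the frequency of adverse outcomes/events does not exceed that expected in infants born at" the trial's gestational ages.

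The Safety section illustrates what is expected with five rates from the study unit, introduced as examples: the "baseline rate of late-onset sepsis in this population is 27"%, and "early-onset sepsis is 1%, death is 15%, BPD is 70% and necrotising enterocolitis is 12"%.

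Under Sample size, "We will recruit 24 infants", and "this number of participants will suffice to demonstrate safety and feasibility". The support given is previous clinical experience with the drug and knowledge of its mechanism. No error rate, margin or precision is stated. Under Summary dosing strategy, 6 infants are treated in Stage 1 and 18 in Stage 2. The section Statistics - clinical covers only summaries of continuously recorded physiological data and their comparison between the two dosages.

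**The concern.** As written, the criterion compares an observed frequency with a fixed number and treats any excess as failure, for every type of adverse event. In 24 infants most observed frequencies will fall above their true rate roughly half the time by chance alone. With several outcomes judged together, failure is the likely result even if the drug does nothing.

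The opposite error is also open. An observed rate below its baseline counts as safe, although in a sample this small it can be compatible with a much higher true rate. The primary conclusion, which is meant to support larger trials, would then depend heavily on chance in either direction, while the Sample size section presents 24 as enough.

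**Working it through.** **Inputs.** n = 24 (Sample size); 18 infants in Stage 2 (Summary dosing strategy); baseline rates p of 27%, 1%, 15%, 70% and 12% (Safety). The article gives no formula behind 24, so there is no planned figure to reproduce. What can be checked is how the stated rule behaves.

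**Step 1. One outcome, no drug effect.** The rule fails when the count X exceeds n × p. With X ~ Binomial(24, p):

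| Outcome | p | Expected count, 24p | Fails at | P(fail) |
|---|---|---|---|---|
| Late-onset sepsis | 0.27 | 6.48 | 7 or more | 48.2% |
| Early-onset sepsis | 0.01 | 0.24 | 1 or more | 21.4% |
| Death | 0.15 | 3.60 | 4 or more | 49.5% |
| BPD | 0.70 | 16.80 | 17 or more | 56.5% |
| NEC | 0.12 | 2.88 | 3 or more | 56.3% |

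**Step 2. At least one of the five.** If independent: 1 − (0.518 × 0.786 × 0.505 × 0.435 × 0.437) = 96.1%. Variations:
- Within-infant latent correlation (simulated): 92.8% at 0.3, 90.5% at 0.5, 87.8% at 0.7, 83.6% at 0.99.
- Expected count rounded to the nearest whole number, independent: 88.0%. Rounded up: 80.1%.
- BPD counted in survivors only: 95.6%. BPD and death mutually exclusive: 98.1%.
- Stage 2 alone (n = 18), independent: 94.8%.
- Under any dependence, the unrounded rule fails at least 56.5% of the time, from BPD alone.

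**Step 3. What a passing result shows.** These are the largest counts that still meet the rule, with exact (Clopper-Pearson) two-sided 95% intervals:
- Death, 3/24 = 12.5%: 2.7% to 32.4%. Twice the baseline is 30%.
- NEC, 2/24 = 8.3%: 1.0% to 27.0%. Twice the baseline is 24%.

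Both intervals include a doubling. This is close to the edge and depends on the confidence level: the one-sided 95% upper limits are 29.2% and 23.98%, just below a doubling. Lower counts do better; 2 deaths in 24 also gives an upper limit of 27.0%, below 30%. Late-onset sepsis is better served: 6/24 has an interval of 9.8% to 46.7%, below the doubled rate of 54%.

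For Stage 2 alone, 2/18 = 11.1% meets both the death and the NEC baselines. Its two-sided interval is 1.4% to 34.7% and its one-sided 95% upper limit is 31.0%, so a doubling of either is not excluded at either level.

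**Step 4. A conventional flagging limit, for comparison.** Flag an outcome when the one-sided 5% exact test against its baseline rejects (the 5% is an assumption). At n = 24 the limits are 11, 2, 8, 21 and 7 events, in the order of the table, with individual false-alarm rates of 3.7%, 2.4%, 2.0%, 4.2% and 1.9%. Overall: 1 − (0.963 × 0.976 × 0.980 × 0.958 × 0.981) = about 13% if independent. The chance of flagging a true doubling is 84% for late-onset sepsis, 43.5% for death and 35% for NEC, so a doubling of death is missed 57% and of NEC 65% of the time.

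**Step 5. Best case.** With zero events the one-sided 95% upper limit is 1 − 0.05^(1/n): 11.7% at n = 24 and 15.3% at n = 18.

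**The case against.** The strongest reply is that the rule computed here is stricter than the authors meant. The five rates are examples, not a list of co-primary tests, and expected frequency could be read as including ordinary variation. A full protocol or analysis plan may supply intervals. This is a pilot with a data safety monitoring board, which reviews adverse incidents after 3 and 6 infants, and moving to Stage 2 also rests on mortality, complications and pharmacokinetics.

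Part of this stands. The 96% is conditional on the literal reading, and the board's reviews limit the consequences during the trial. But the Abstract and the Safety section both state the end-of-trial criterion, neither gives a tolerance, and the sufficiency claim is made outright. Since the wording covers all adverse events and also their severity, outcomes beyond the five would add further ways to fail.

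Three stronger readings are tempting and are not supported:
- **That failing the rule declares the drug harmful.** The text says only when the drug will be considered safe; failing means not shown safe. Counts and intervals would remain interpretable.
- **That the baselines are biased.** Enrolment is restricted to infants born on site, has exclusions, and assumes "a recruitment rate of 20-25% of eligible babies". Selection is plausible, but the article says the rates describe this population and does not give their denominators. The size and direction of any bias are unknown.
- **That a lower-limit flagging rule cures the problem.** Step 4 shows that it exchanges frequent false alarms for frequent missed harm.

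**Conclusion.** The concern holds for the criterion and for the sufficiency claim. Read literally, a drug with no effect would fail about 96% of the time if outcomes are independent and about 80-90% under strong correlation or rounded thresholds. In the other direction, at the two-sided 95% level a result that just meets the rule does not exclude a doubling of death or NEC. The statement that 24 infants suffice to demonstrate safety is not supported.

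The failure probabilities assume that the five example rates are exactly known and are the whole list, and that any excess counts as failure. This is a stated rule and a stated property of the design, not detail left to another document. It does not show that the drug would be declared harmful, or that the baselines are wrong.

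**What to change.** 1. In the Abstract and the Safety section, restate the criterion. Report each listed outcome with its exact confidence interval against its baseline, overall and for the 18 Stage 2 infants, and draw the conclusion from the interval, not from whether the point estimate lies above the baseline. If a formal flagging limit is wanted, state both its overall false-alarm rate and its chance of missing a doubling, as in Step 4.
2. In Sample size, replace the sufficiency claim with the precision achieved: zero events would exclude rates above 11.7% with 24 infants and above 15.3% with 18 (one-sided 95%). Describe the result as preliminary safety data.
3. Also report death-or-BPD, because an infant who dies early cannot go on to develop BPD and excess mortality could appear as less BPD.
4. State as a limitation that enrolled infants may differ from the benchmark population, by an unknown amount.

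The cost is rewording and a few extra intervals. Recruitment, dosing and data collection do not change. The drawback is that the trial's stated claim becomes less favourable.

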### Estimated duration of individual subject participation

Anakinra treatment commences at 3-24 hours of postnatal life and ceases on postnatal day 21. Treatment will continue until day 21 unless one of the following occurs: a suspected unexpected serious adverse reaction; acute kidney injury (which would increase dose-normalised exposure in the unlikely setting of immature non-renal clearance); neutropenia; or elevation of liver enzymes (details below). To monitor for these events and as part of standard care, the following blood tests will be sent to the routine pathology laboratory on days 1, 3, 7, 14, and 22 after starting IL-1Ra infusions in addition to plasmatic and cellular immunity analysis: full blood count, liver enzyme tests, urea, electrolytes and creatinine.

Treatment will cease if consent is withdrawn, in which case consent will be sought for the infant to remain enrolled and data collection to continue to enable intention-to-treat analysis. Rates of withdrawal of consent will be monitored to detect differential dropout, which can bias clinical trial results and reduce the power of the trial to detect important differences. Treatment will also cease if death is imminent and the treating team with the parents have made the decision to redirect care.

Collection of data will continue until 2 years of age, with a review at 3 months corrected age (i.e. 3 months after the infant reaches an age that equates to 40^0^ weeks GA) in the Early Neurodevelopmental Clinic (including a Prechtl’s general movements assessment), and a neurodevelopmental review at 2 years.

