### Summary dosing strategy

For Stage 1, six infants will receive 1.0 mg/kg IV given alternate daily from day 1 to day 21 after birth. In the event of acute kidney injury (AKI), detection during blood monitoring within the 3 weeks of treatment, anakinra treatment will be halted until renal function has recovered as defined below.

After completion of Stage 1, the Investigators and the data safety monitoring board (DSMB) will conduct an interim analysis, including assessment of mortality and rate of complications of prematurity, and comparison of observed exposure with the predicted exposure estimated from the population PK simulation. If appropriate, with confirmation of mature non-renal clearance within the first cohort of 6 infants, Stage 2 will administer 1.5 mg/kg per day for the remaining 18 infants. Furthermore, dosing will not need to be withheld in the setting of acute kidney injury (AKI) if non-renal clearance is confirmed to be mature from birth.

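### The 15% death benchmark is defined by gestational-age band only, not by the infants the trial can enrol and dose, so it is probably too lenient; for the other outcomes the direction is uncertain

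*Protocol article*

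**What the plan says.** The Abstract (Methods and analysis) calls anakinra safe if the frequency of adverse outcomes "does not exceed that expected in infants born at 24^0^-27^6^ weeks GA". Definitions - Safety makes this the primary-objective definition: the regimen is completed "without any adverse events of greater frequency or severity than expected to be observed in this high-risk population". As examples it adds that "at Monash Newborn the baseline rate of late-onset sepsis in this population is 27%, early-onset sepsis is 1%, death is 15"%, and that "BPD is 70% and necrotising enterocolitis is 12"%.

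The infants who can contribute data are narrower than that band:

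- Inclusion criteria: born on site.
- Exclusion criteria: imminent death, severe abnormalities, "substantial pre-/perinatal compromise", severely and permanently compromised renal function, and any other condition judged to confound the results.
- Estimated duration of individual subject participation: "Anakinra treatment commences at 3-24 hours of postnatal life", so an infant must be alive then.
- Duration of trial: 20-25% of eligible infants are expected to be recruited.

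On size, the article says "We will recruit 24 infants", six in Stage 1, and if appropriate "Stage 2 will administer 1.5 mg/kg per day for the remaining 18 infants". Under Summary dosing strategy, the review after Stage 1 includes mortality and the rate of complications of prematurity.

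**The concern.** In a single-arm trial the expected rate stands in for the control group. An infant who dies in the delivery room, or is moribund on day 1, can count in a death rate for the gestational-age band but cannot enter the trial. If such deaths are in the 15%, treated infants are compared with a sicker group, and some excess mortality on treatment could be read as normal. That reading would feed the review before the second dosing stage and the final safety statement.

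The benchmark is also one figure per outcome across four gestational weeks. With 24 infants, the mix of weeks enrolled may differ from the mix behind the figure. Finally, the 70% for BPD carries no definition, while Safety monitoring records BPD both as yes/no and by Jensen grade.

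**Working it through.** **Inputs from the article.** Death 15%, late-onset sepsis 27%, necrotising enterocolitis 12%, BPD 70%; N = 24. The 24 is justified in words only (no error rate, margin or target effect), so there is no calculation to reproduce.

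**Input not in the article.** *s*, the share of baseline deaths in infants who could not be enrolled or dosed. Assumed range: 10% to 50%.

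**Step 1: expected deaths at the stated rate.** 24 × 0.15 = 3.6. Read literally, four or more deaths exceed expectation.

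**Step 2: death rate after removing the unenrollable deaths.** Restricted rate = 0.15(1 − s) / (1 − 0.15s). For s = 20%: 0.12 / 0.97 = 12.4%.

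| s | restricted rate | expected in 24 | 15% ÷ restricted rate |
|---|---|---|---|
| 10% | 13.7% | 3.3 | 1.09 |
| 20% | 12.4% | 3.0 | 1.21 |
| 33% | 10.5% | 2.5 | 1.42 |
| 50% | 8.1% | 1.9 | 1.85 |

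The last column is the true relative increase that would bring the death rate up to exactly 15%.

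**Step 3: why these rates are lower limits.** The formula removes only infants who die. If excluded infants who survive make up a fraction e of the band, the denominator becomes 1 − 0.15s − e and the rate moves back up. With e = 5%, s = 20% gives 0.12 / 0.92 = 13.0% and s = 50% gives 0.075 / 0.875 = 8.6%. The restricted rate is below 15% exactly when mortality among the removed infants exceeds 15%. That is likely when the removed group includes those dying imminently or before dosing.

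**Step 4: effect on the literal rule.** Suppose treatment doubled the restricted death rate. The binomial probability of four or more deaths in 24 is then 0.93, 0.88, 0.78 and 0.56 for s = 10%, 20%, 33% and 50%. With the threshold set from the restricted rate (4, 3, 3 and 2 deaths) it is 0.93, 0.96, 0.91 and 0.92. Part of this gain is bought with false flags: with no drug effect, the restricted thresholds flag with probability 0.42, 0.58, 0.47 and 0.59, against 0.42, 0.35, 0.24 and 0.13 for four or more deaths. Matching the benchmark corrects the reference point. It does not repair a rule that has no margin.

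**Step 5: the other outcomes.** If the infants removed by early death had none of these events, the rate among the rest is rate / (1 − 0.15s). Over s = 10% to 50%:

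- late-onset sepsis: 27% becomes 27.4% to 29.2%
- necrotising enterocolitis: 12% becomes 12.2% to 13.0%
- BPD: 70% becomes 71.1% to 75.7%

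On this account alone the stated rates are slightly strict. Excluding compromised infants may lower the true rates instead. The article has nothing to settle the net sign.

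**Step 6: gestational-age mix.** With purely illustrative death rates of 30%, 18%, 10% and 6% at 24, 25, 26 and 27 weeks:

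- older mix (10/20/30/40%): 0.030 + 0.036 + 0.030 + 0.024 = 12.0%
- younger mix (35/30/20/15%): 0.105 + 0.054 + 0.020 + 0.009 = 18.8%

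The shift can go either way and is as large as that from eligibility.

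**The case against.** The strongest reply is that silence is not proof. The rates are given for this population and introduced as examples, and a full protocol or analysis plan may describe how the reference cohort was built. This stands in part. A reader might infer that the figures are averages over the whole unit; the wording does not support that, since both statements tie them to the trial's gestational-age band. The missing calendar period and denominator are no finding in an article. What remains is that the article names its comparator by gestational age alone while its own criteria define a narrower group.

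A reader might also infer that the whole comparison leans towards declaring safety. Steps 5 and 6 show that the documents do not support this beyond death. Nor does the low recruitment fraction show that enrolled infants are healthier, because nothing is said about which families consent.

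It can also be objected that the shift is small beside sampling noise: 3.6 expected deaths become 3.0 or 2.5, and a doubling is still flagged with probability 0.88 or 0.78 at s = 20% or 33%. That is fair. But a systematic error in the only comparator does not average out, and it can be removed cheaply.

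Last, a reader might fear that a difference in gestational age between stages would be taken for a dose effect. The only between-stage comparison specified (Statistics - clinical) concerns continuously collected physiological data, not clinical events, and the DSMB neonatologists can take gestational age into account. That harm is not part of the plan.

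**Conclusion.** The point holds for death. The stated benchmark is not matched to infants who can be enrolled and dosed, and the mismatch probably makes 15% too lenient. If 10-50% of baseline deaths were in infants who could not be enrolled or dosed, the comparable rate is at lowest 13.7% to 8.1%, and up to a 1.1- to 1.85-fold excess could pass as expected. These are upper limits on the distortion for each assumed share, and the true share cannot be found in the article. For sepsis, necrotising enterocolitis and BPD, the conclusion is only that the benchmark is unmatched and the direction unknown. Lack of gestational-age standardisation adds an error of either sign. The change should be made, but the design does not fail without it.

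**What to change.** Derive the expected rates from existing unit data, pooling several years, for infants born on site at 24+0 to 27+6 weeks, with the trial's exclusions applied as far as records allow and restricted to those alive at the dosing window. Standardise the expected counts to the gestational-age distribution actually enrolled. Report observed against expected events with exact intervals, and use one BPD definition in both the benchmark and the trial.

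The cost is a database query and a few lines in the analysis plan; treatment and follow-up do not change. The drawbacks are some imprecision in week-specific rates, exclusions that old records may capture only partly, and probably a lower, less favourable expected death rate. The article's forecast of 8-15 enrolled a year at 20-25% recruitment implies about 32 (8 / 0.25) to 75 (15 / 0.20) eligible infants a year. That is roughly 8 to 19 per gestational week if evenly spread (an assumption), hence the need to pool years.
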